## Abstract

**Background:**

Chronic tendinopathy is a significant problem particularly in active populations limiting sporting and occupational performance. The prevalence of patellar tendinopathy in some sports is near 50% and the incidence of lower limb tendinopathy is 1.4% p.a. in the UK Military. Management includes isometric, eccentric, heavy slow resistance exercises and extracorporeal shockwave therapy (ESWT). Often these treatments are inadequate yet there is no good evidence for injection therapies and success rates from surgery can be as low as 50%.

High Volume Image Guided Injection (HVIGI) proposes to strip away the neovascularity and disrupt the nerve ingrowth seen in chronic cases and has shown promising results in case series. This study aims to investigate the efficacy of HVIGI in a randomised controlled trial (RCT).

**Methods:**

RCT comparing 40ml HVIGI, with or without corticosteroid, with a 3ml local anaesthetic sham-control injection. Ninety-six participants will be recruited. Inclusion criteria: male, 18–55 years old, chronic Achilles or patellar tendinopathy of at least 6 months, failed conservative management including ESWT, and Ultrasound (US) evidence of neovascularisation, tendon thickening and echogenic changes. Outcome measures will be recorded at baseline, 6 weeks, 3, 6 and 12 months. Primary outcome measures include The Victoria Institute of Sport Assessments for Achilles and patellar tendinopathy (VISA-A and VISA-P) and VAS pain. Secondary outcome measures include Modified Ohberg score, maximum tendon diameter and assessment of hypoechoic appearance on US, and Functional Activity Assessment.

**Discussion:**

Despite previous interventional trials and reviews there is still insufficient evidence to guide injectable therapy for chronic tendinopathy that has failed conservative treatment. The scant evidence available suggests HVIGI has the greatest potential however there is no level one RCT evidence to support this. Investigating the efficacy of HVIGI against control in a RCT and separating the effect of HVIGI and corticosteroid will add high level evidence to the management of chronic tendinopathy resistant to conservative treatment.

**Trial Registration:**

EudraCT: 2015-003587-36 3 Dec 2015

## Background

Lower limb tendinopathy is a significant problem especially in the sporting population. The reported incidence increases from 1.85/1000 p.a. in the Achilles amongst the general population to 7.4% per month in marathon runners [1, 2]. In the patella prevalence is 10–15% in volleyball and rugby players and up to almost 50% in masters athletes [3–5]. Military personnel by the nature of their work are a physically active and sporting population. From the UK military Primary Care database incidence of lower limb tendinopathy is estimated at 1.4% p.a. representing a significant cause of morbidity. This represents a significant burden to the Armed Forces in terms of occupational and operational effectiveness. The unpredictable nature of tendinopathy by virtue of its poor correlation between pain, function and pathological stage adds uncertainty to workforce planning and career development for the individuals affected.

The tendinitis model in use up to the 1990s has been superseded [6]. A continuum model for tendinopathy whereby abnormal load is seen as the primary cause and optimal load management is seen as the primary treatment is now well established and accepted [7]. This model described by Cook and Purdam [8] based on histological findings provides the framework on which current best practice is designed and areas for further research are targeted. There is increased proteoglycan, ground substance and collagen separation with cells taking on a more chondrotic shape but absence of typical inflammatory mediators on traditional histology. Neovascularisation occurs as the pathology progresses and is thought to be associated with nerve ingrowth and pain. With this change of understanding many treatments have been tried, some with more success and better evidence than others.

Eccentric Loading Exercise *(EL)* is a well-established treatment in Achilles tendinopathy and has been developed successfully to treat other tendinopathies [9, 10]. Early trials by Alfredson [11, 12] were in older patients (mean age = 44) with a chronicity that would place them in the degenerate phase of Cook and Purdam’s continuum. Unmodified EL is not effective for insertional tendinopathy [13]. Heavy Slow Resistance Exercise (HSR*)* is an alternative to EL. Kongsgaard et al’s [14] RCT investigating patellar tendinopathy showed similar results for HSR and EL in terms of pain and function. HSR also yielded increased collagen network turnover and greater satisfaction than EL in a younger population (mean age = 32).

Extracorporeal Shockwave Therapy (ESWT) showed initially promising results in supraspinatus, elbow and heel tendinopathies [15]. Furia’s [16] trial of 68 patients showed superior results with ESWT compared to traditional therapy controls in insertional Achilles tendinopathy. Wang [17] et al. reported impressive results in favour of ESWT v. control in patellar tendinopathy with statistically significant differences in VISA-P scores at 2–3 year follow up. ESWT has been concluded in reviews by Wiegerinck [18] and van Leeuwen [19] to be a safe effective treatments for insertional Achilles and patellar tendinopathies respectively. It should be noted Zwerver [20] found no effect of ESWT in an RCT of 62 participants with patellar tendinopathy. Though they conclude the continued sports participation of mostly reactive to disrepair stage tendinopathies treated could explain the lack of effect and that ESWT may still be effective.

Unfortunately a number of patients still fail to respond to EL, HSR or ESWT. What to do next is a clinical dilemma with insufficient evidence to guide. Surgery remains an option but with success rates as low as 50% [21] there is a desire to find safe effective treatment that bridges the gap from conservative management.

High Volume Image Guided Injection (HVIGI) has been proposed to remove neovascularisation and disrupt nerve ingrowth [22]. Whilst there is no universally accepted pain model in tendinopathy there are well established mechanisms for associating angiogenesis with neoneuralisation including shared genetic pathways and neurotrophic effects of Vascular Endothelial Growth Factor (VEGF) [23]. Increased substance P positive nerve fibres may provide a nociceptive stimulus coupled with decreased pain modulation by noradrenaline [24]. Prolonged expression of substance P may stimulate the hypercellularity and altered morphology of tenocytes as well as stimulating endothelial cells [25]. It is anticipated a shearing or compressive effect of HVIGI by using the neovessels as a target area may achieve disruption of these nerve fibres. Such mechanical damage may act synergistically with other mechanisms for example neurotoxicity and vasoconstriction caused by the initial local anaesthetic bolus [26].

Table 1 outlines the HVIGI studies to date. The studies indicate positive results but all lack control groups and causality of benefit cannot be identified from these study designs. There is variation in duration of follow up and the use of corticosteroid (CS) making results of this group of studies difficult to interpret.

**Table 1 Tab1:** Summary of HVIGI studies

Study	Intervention	Control	+/− VAS Pain	+/− Function eg VISA-A/P
Achilles tendinopathy				
Chan 2008 [68]	*N* = 30 10ml 0.5% Bupivacaine 25mg Hydrocortisone 40ml N Saline	No control	*N* = 21 @4w -51mm	*N* = 21 @4w VISA-A +31.4
Humphrey 2010 [69]	*N* = 11 10ml 0.5% Bupivacaine 25mg Hydrocortisone 40ml N Saline	No Control		@3w VISA-A +38 (*P* < 0.001) NeoVasc reduced 3 to 1.1 Tendon diam 8.7 to 7.6mm
Restighini 2012 [70]	*N* = 32 5ml 1% Lidocaine 25mg Hydrocortisone Up to 40ml N Saline	No Control	@4w -34mm @3m -37mm	@4w VISA-A +26.5 @3m VISA-A +28.7 NeoVasc reduced 2 to 0.2
Maffuli 2013 [71]	*N* = 94 10ml 0.5% Bupivacaine 25mg Aprotinin up to 40mls N saline	No Control		@12m VISA-A +32.9 (*P* = 0.003)
Wheeler 2014 [72]	*N* = 16 10ml 1% Lidocaine 40ml Saline	No Control	@347d −6.1/10 (*P* = 0.001)	@347d VISA-A + 41 (*P* = 0.001)
Wheeler 2016 [73]	*N* = 34 10ml 1% Lidocaine + 40ml Saline V 10ml 1% Lidocaine + 20ml Saline	No Control	@281d −4.6/10 (*P* < 0.01) 50ml Group	@281v271d VISA-A +33.4 and + 6.94 in 50ml and 30ml group respectively (*P* = 0.002)
Patellar tendinopathy				
Crisp 2008 [74]	*N* = 9 10ml 0.5% Bupivacaine 25mg Hydrocortisone 40ml N Saline	No control	@2w Sig. improve.	@9m VISA-P +22
Morton 2014 [22]	*N* = 20 10 ml 0.5% Bupivacaine 25mg hydrocortisone 30ml N saline	No Control		@12w–9m VISA-P +19 (*P* < 0.01)
Maffuli 2016 [75]	*N* = 44 10ml 0.5% Bupivacaine 62500 IU Aprotinin 40ml N saline	No Control	@15m -63mm (*P* = 0.01)	@15m VISA-P +29.3 (*P* = 0.003)

*VISA-A* Victoria Institute of Sport Assessment-Achilles, *VISA-P* Victoria Institute of Sport Assessment-Patella, *VAS* Visual Analogue Scale, *NeoVasc* Grade of Neovasculatity, *IU* International Units, *m* months, *w* weeks, *d* days

The primary objective of this study therefore is to identify through a RCT the effectiveness of HVIGI using injectable saline (40ml) in combination with local anaesthetic with/without injected CS compared to a sham-control injection in patients with chronic tendinopathy unresponsive to conservative therapies.

The hypotheses are that HVIGI in both the presence and absence of CS will be superior to control and that HVIGI without CS will be non-inferior to HVIGI with CS.

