### Sample size

The effect size *f* has been calculated along with the overall predicted sample size calculation using GPower (University of Dusseldorf, GER) [33]. The Minimum Clinically Important Difference (MCID) in the VISA-P score in athletes with patellar tendinopathy who underwent conservative management was calculated by Hernandez-Sanchez [34] to be 12.6 (*n* = 90 baseline VISA-P = 50.1 (SD = 18.4). The effect size *f* of 0.3228096 was combined with an α-level of 0.05 and power of 0.8 in a priori power calculation for an ANOVA, fixed effects, omnibus one way test predicting an initial sample size of 96. The calculation was repeated so that addition of a suspected covariate (percentage adherence to the standardised rehabilitation protocol) could be considered in ANCOVA again a sample size of 96 was predicted. Further calculations were made to allow using repeated measures, between factors ANOVA assuming correlation of 0.5 among repeated measures this returned a smaller total sample sizes of 75 for primary outcome measures (baseline and 6 month follow-up) and 60 for secondary outcome measures (baseline, 6 weeks, 3,6 and 12 month follow-ups). 108 participants with either Achilles or patellar tendinopathy will be recruited to allow for a 10% drop out rate.

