### Statistical analyses

Demographic data over the 3 RCT groups will be compared. This will include the risk factors to be analysed as part of a correlational study including age, obesity, smoking, blood group, hypertension and family history. Parametric assumption checks will be made and one-way ANOVA used to check for statistical differences that may have occurred by chance at baseline. Where necessary ANCOVA will be used to correct differences across the groups. The adherence to rehabilitation score will be considered as a covariate.

The primary outcome data will be compared between groups at baseline and 6 months. Individual outcome measures for each group will be analysed to check parametric assumptions. For primary and secondary outcome measures a repeated measures, between factors ANOVA (time x intervention) will be used to look for significant difference. Groups will then be compared against each other using *post hoc* pairwise comparisons using SPSS software and effect sizes calculated.

A protocol deviation log is to be kept so that unanticipated trends can be analysed. The proportion of missing data will be reported with reasons where possible. Missing data will be handled using multiple imputation calculated in SPSS. A minimum of 5 imputations will be used. Results for completed cases will be compared to those based on multiple imputation and reported in accordance with the guidance proposed by Sterne et al. [35].

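### Non-inferiority of HVIGI without corticosteroid is a stated hypothesis, but the analysis and the sample size provide only tests for difference, which cannot establish it

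*Protocol article*

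**What the plan says.** The Background section ends with three hypotheses. Two are superiority claims: HVIGI with corticosteroid (CS) and HVIGI without it will each beat the sham-control. The third is that "HVIGI without CS will be non-inferior to HVIGI with CS". The primary objective in the same section is HVIGI, with or without CS, against sham. The abstract's Discussion and the closing paragraph of the main Discussion add that separating the steroid effect from the HVIGI effect is part of what the trial is for.

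Under Statistical analyses, the method for primary and secondary outcomes alike is that "a repeated measures, between factors ANOVA (time x intervention) will be used to look for significant difference". The next step is: "Groups will then be compared against each other using *post hoc* pairwise comparisons using SPSS software and effect sizes calculated".

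Under Sample size, an effect size f of 0.3228096 "was combined with an α-level of 0.05 and power of 0.8", for an "omnibus one way test predicting an initial sample size of 96". Three further calculations follow: ANCOVA, and repeated measures with two and with five time points. All four are for differences. The 12.6-point MCID for VISA-P serves only to derive f and is not used as a margin.

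The primary outcomes are VAS pain and VISA-A or VISA-P, both at 6 months.

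**The concern.** A test for difference takes equality as its null hypothesis. Rejecting that null in favour of CS would count against non-inferiority. Failing to reject it shows only that the data did not separate the arms, which becomes more likely as the trial gets smaller or noisier. Non-inferiority needs the opposite null, a deficit of at least some stated margin, rejected by a confidence limit. Nothing in the stated analysis does that, so the third hypothesis and the analysis written for it do not match.

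At stake is the conclusion about leaving out the steroid. The Governance section sends the trial report to the committee that updates Defence rehabilitation guidelines, so an unsupported statement on this comparison could reach practice. The two superiority hypotheses are not affected.

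**Working it through.** **Inputs from the protocol article.** MCID 12.6 and SD 18.4 (VISA-P), alpha 0.05, power 0.80, f = 0.3228096, correlation among repeated measures 0.5, equal allocation to three arms, 96 analysed (32 per arm), 108 recruited (36 per arm).

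**Assumptions.** The VISA-P SD applies to VISA at 6 months in both tendons. Margins of 12.6, 8 and 6.3 points are illustrative, because the article gives none. Non-inferiority is tested at one-sided 0.025. The article gives no SD for VAS, so VAS cannot be calculated.

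**1. The plan's own figure.** Take two equal arms and a third 12.6 points away, for example means 0, 12.6, 12.6:
- mean = 8.4; variance of the means = (8.4² + 4.2² + 4.2²)/3 = 35.28; square root = 5.94
- f = 5.94/18.4 = 0.3228, as stated
- noncentrality at N = 96: 0.3228096² × 96 = 10.00; with 2 and 93 degrees of freedom, power = 0.802

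N = 96 reproduces, as do 96 for ANCOVA and 75 and 60 for repeated measures. Dropout gives 96/0.9 = 107, and 108 is the next multiple of 9, the envelope batch size. The sample size is right for the omnibus test it describes.

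**2. Precision of the steroid comparison.** Half-width of the 95% CI = t × SD × √(2/n).
- Unadjusted, n = 32: 1.999 × 18.4 × √(2/32) = 1.999 × 4.60 = 9.2
- Baseline-adjusted: SD = 18.4 × √(1 − 0.5²) = 15.9; half-width = 1.999 × 3.98 = 8.0
- With 36 per arm: 8.6 unadjusted, 7.5 adjusted

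At correlation 0.5 a change score has SD 18.4 × √(2 × (1 − 0.5)) = 18.4. The unadjusted figure therefore also fits a comparison of change from baseline, which is what a time-by-intervention contrast over two time points amounts to.

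**3. Chance that the difference test is non-significant when HVIGI without CS is truly worse.** Noncentral t, 62 degrees of freedom, noncentrality = deficit/(SD × √(2/32)), two-sided 0.05. For 9 points: 9/4.60 = 1.96 unadjusted, 9/3.98 = 2.26 adjusted. The Bonferroni column (three pairs, 0.05/3) is included because the article does not name a post hoc procedure.

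| True deficit (VISA points) | SD 18.4 | SD 18.4, Bonferroni | SD 15.9 | SD 15.9, Bonferroni |
|---|---|---|---|---|
| 6.3 | 73% | 85% | 66% | 80% |
| 9 | 51% | 69% | 40% | 57% |
| 12.6 | 23% | 39% | 12% | 24% |

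**4. Power of a real non-inferiority test at true equality, 32 per arm.** Noncentrality = margin/(SD × √(2/32)).

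| Assumed margin | SD 18.4 | SD 15.9 |
|---|---|---|
| 12.6 | 77% | 88% |
| 8 | 40% | 51% |
| 6.3 | 27% | 34% |

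For 80% power, a margin of 12.6 needs 34 per arm unadjusted or 26 adjusted. A margin of 6.3 needs 134 or 101.

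**The case against.** A reader might infer that the investigators intend to call a non-significant result non-inferior. The article does not say so. It states no decision rule for this hypothesis, and it plans to report effect sizes, so some estimation is already intended. That stands: the misreading is left open, not prescribed.

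It can also be said that a margin and confidence-limit rule are often left to a full protocol or SAP, and the article says the full protocol may be requested. So the missing margin is not a fault by itself. This does not remove the point, because the article is not silent on method. It commits all primary and secondary outcomes to a difference test and sizes the trial only for difference tests, and neither fits the hypothesis it states.

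The comparison is not the primary objective, which is HVIGI against sham. That limits the reach of the problem, although separating the steroid effect is a declared aim.

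Finally, the unadjusted figures at 32 per arm are the harsher ones. Baseline adjustment, or 36 per arm, improves them. A true 12.6-point advantage for CS at 6 months would also run against the article's own review, which finds no intermediate or long-term steroid benefit. Both remarks are fair, and the ranges above allow for them. Even with 36 per arm and adjustment, a 9-point deficit goes undetected 34% of the time and power at a 6.3-point margin is 38%.

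**Conclusion.** Wrong as written. The article states a non-inferiority hypothesis and fixes an analysis that cannot support it. This conclusion rests on the text alone and needs no numerical assumption.

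The size does depend on assumptions (32 per arm, SD 18.4 or 15.9, illustrative margins). A non-significant result would be compatible with a sizeable deficit, since the interval extends 8.0 to 9.2 points either side of the estimate. The planned size comes close to or exceeds 80% power for non-inferiority only if the margin is about as wide as the full MCID. At half the MCID, power is roughly 27% to 34%. The sample size calculation itself contains no error, and the superiority comparisons with sham stand apart from this point.

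**What to change.** **Preferred.** In the hypotheses (Background) and in Statistical analyses, restate the third hypothesis as estimation. Report the baseline-adjusted 6-month difference, HVIGI without CS minus HVIGI with CS, with its 95% CI for both VISA and VAS. State that a non-significant difference will not be called non-inferior.

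**If the non-inferiority claim is kept.**
- Fix and justify a margin for each primary outcome. VAS needs its own, and the cited 12.6 is a VISA-P figure while Achilles patients are also enrolled.
- Do this before anyone, including the Chief Investigator, examines outcome data by arm. A deadline of formal unblinding would not be enough, because the Chief Investigator knows the allocations, holds the outcome data and analyses accruing data for the monitoring committee.
- Conclude non-inferiority only from the confidence limit on the unfavourable side against that margin: the lower limit for VISA and the upper limit for VAS, given the subtraction order above.
- State the power that the margin gives at the planned size.

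**Cost.** The preferred change is wording only and needs no extra patients, but the steroid comparison is stated less favourably. Keeping the claim also needs no extra patients provided the resulting power is accepted and reported; with a margin well below 12.6 that power would be low.

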## Methods/Design

### Double blind Randomised Control Trial (RCT)

Low volume (3ml) US guided subcutaneous Local Anaesthetic (LA) sham-control injection.orHVIGI: Saline + Local Anaesthetic (LA). Total volume 40ml.orHVIGI: Saline + LA + CS. Total volume 40ml.

#### Participants inclusion/exclusion criteria

##### Inclusion criteria

Male patients with either Achilles or patellar tendinopathy of at least 6 months chronicity who have failed best practice management (Table 2) including EL, HSR and ESWT aged 18–55 and US evidence of neovascularisation, tendon thickening and echogenic changes will be included in the study. Patients must be medically unfit for their full military role. The level of function relating to military medical grading relates to the patient’s individual role. The relationship between this and VISA scores will be explored as part of this research. The diagnostic guide used for initial diagnosis in primary care is provided in Table 3. Diagnosis is confirmed by a Sport and Exercise Medicine Consultant with the additional US criteria above.

**Table 2 Tab2:** Defence rehabilitation Achilles and Patellar tendinopathy best practice management pathway

Tendon loading stage	Type of contraction	Reps/Sets/Holds	Aim of phase	Progression criteria	
				Load tolerance tests	Outcome measures
Stage 1 – Low Load Daily exercise	Isometric (may avoid painful range initially)	5x 15–60 s holds Repeated 4x daily 5 days/week	Inhibit cortical interpretation of pain. Tendon adaptation to load	Able to move body weight double leg with pain less than 3/10 eg, squat, calf raise	Numeric Rating Scale or Visual Analogue Scale On first waking On activity After activity VISA A/P 6 weekly intervals
Stage 2 – Medium Load Alternate days with Stage 1	Eccentric/Concentric (may avoid painful range initially)	3x 10–12 3 s Eccentric / 3 s Concentric	Inhibit cortical interpretation of pain Musculo-tendinous adaptation to load.	Able to move body weight single leg with pain less than 3/10, eg single leg squat/single leg calf raise	
Stage 3 – High Load Every third day with Stage 1 and 2 on days inbetween	Eccentric/ Concentric Heavy Slow Resistance	3x15 (reduced progressively as weight increased) 3 s Eccentric /3 s Concentric 60% 1RM (3x15 reps) progressed to 85% 1RM (3x6 reps) in week 12	Musculo-tendinous adaptation to load through controlled movements	Able to perform low level plyometric test with less than 3/10 pain, eg repeated small hop or split jump	
	Eccentric Loading	3x15 (double leg, single leg, weighted) Up to 10 s eccentric phase			
Stage 4 – High Load In place of Stage 3 loading, with Stage 1 and 2 inbetween	Plyometric	Restricted to 60 foot contacts when introduced. eg. 3x10 Forward hops 3x10 Single leg hops Increased to 80 foot contacts	Elastic loading of Musculotendinous unit.	Able to perform high level plyometric test e.g. repeated maximal hop and multidirectional hop.	

*RM* Repetition Maximum, *VISA-A* Victoria Institute of Sport Assessment-Achilles, *VISA-P* Victoria Institute of Sport Assessment-Patella

**Table 3 Tab3:** Diagnostic guide

	Achilles tendon (inc Insertional)	Patella tendon
Causative factors	Common in running sports and may have been precipitated by a change in training load (volumes, duration or intensity).	Common in running, tabbing and jumping sports and may have been precipitated by a change in training load (volumes, duration or intensity).
Pain site	Localised tenderness in mid portion of Achilles (2–6cm from insertion) or at insertion.	Pain at inferior pole of patella.
Pain pattern	Pain may occur at start of activity and then ease, or may increase with duration of activity. Pain after period of rest or on waking.	Pain may occur at start of activity and then ease, or may increase with duration of activity. Pain after period of rest or on waking.
Palpation findings	Localised tenderness in mid portion of Achilles (2–6cm from insertion) or at insertion.	Focal pain on palpation.
Provocation and Load Tolerance Tests	Calf raise Small hop Repeated hop Repeated hop Multidirectional Maximal forward hop	Leg extension Single leg decline squat Small hop Split jump Maximal hop

